#### Data management

We perform double data entry and range checks for data values. Data quality management also includes data cleansing (completeness, consistency, duplicates) and validation of data against standard statistical measures. Co-investigator meetings were held monthly during the recruitment phase and then quarterly.

#### Onsite-research team

The members of the onsite-research team facilitate and coordinate the study activities in the rehabilitation centre. They provide intervention measures and collect data as required by the protocol. They provide information for the PI and the team members who are responsible for administration, randomization and analysis.

#### Confidentiality

For the statistical analysis, personalized data is documented only in the rehabilitation centre. Solely, pseudonymized data is sent to the Institute for Medical Informatics, Biometry and Epidemiology (IMIBE) for analysis. All employees are familiar with quality-assured data collection, data monitoring and documentation.

#### Plans for collection, laboratory evaluation and storage of biological specimens for genetic or molecular analysis in this trial/future use

This study does not involve collecting and storing biological specimens for storage in the current trials and for future use in ancillary studies.

### Patient/public involvement

We conduct structured patient interviews to evaluate the patient’s experience with the intervention. Public involvement takes place in the course of dissemination of generally understandable study results.

### Statistical methods

#### Statistical methods for primary and secondary outcomes

The statistical evaluation is carried out using the statistical software SPSS (IBM SPSS Statistics, version 29). The confirmatory analysis to measure the effect of the intervention will be carried out as an intention-to-treat analysis, i.e. all participants who are randomized are included in the statistical analysis and analysed according to the group they were originally assigned. Additional analyses will focus on secondary outcomes as well as associations between independent and dependent variables.

Fasting diaries will be analysed using in-house nutrition information. The mean daily caloric intakes will be computed.

The WHO-5 uses a 6-point Likert scale ranging from 0 = “at no time” to 5 = “all of the time”. The sum of these answers is multiplied by 4; scores of 50 or lower suggest that participants might suffer from depression.

Between-group differences at baseline will be tested using analysis of variance (ANOVA). To answer the primary research question, the mean difference in weight loss between the two groups is compared using analysis of variance (ANOVA), a two-tailed *t*-test, or Spearman’s correlation coefficient, respectively. Chi-square tests are used to compare proportions. All continuous outcomes will be modelled using linear regression. We will analyse the effect of fasting while taking into account periods of fasting and calorie intake from the fasting diaries. All statistical tests assume a two-sided significance level of 0.05.

Guided interviews are transcribed and coded by two independent researchers along an open coding scheme using qualitative content analysis by Mayring [14] via the software MAXQDA (VERBI GmbH, Berlin, Germany). Qualitative content analysis aims at classifying qualitative data into categories of similar connotation.

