#### Sample size

A before-and-after comparison between the intervention group (IG) and the control group (CG) will be used for the evaluation. Follow-up values were assessed at t1, t2 and t3. Regarding the primary outcome, the intervention is considered effective if mean difference in weight loss after 4 weeks (t1) in the IG is at least 2% higher than in the CG compared to baseline (t0). The standard deviation of mean difference is estimated at 3.5 kg. The significance level should be 5%. In order to demonstrate difference in weight with a power of 80%, a two-tailed *t*-test requires a total of 100 patients (50 per group).

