### Assignment of interventions: allocation

#### Sequence generation

As soon as the patient gave written consent, randomization was performed. Randomization took place at individual level, i.e. every single patient was assigned either to the IG or to the CG. A statistician who is not involved in the study generated the randomization list using computer-generated random numbers.

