#### Implementation

After eligibility screening took place at initial admission examination (t0) involving medical history review, physical exams and laboratory tests, two trained members of the research team enrolled patients. To minimize the effect of bias, the random allocation sequence remained concealed from those enrolling patients into the study.

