#### Methods for additional analyses

We will analyse the effect of sociodemographic and clinical variables on the primary outcome as well as the effect of periods of fasting and calorie intake. Additionally, stratified analysis will be performed for those who completed t2 and t3 follow-up. All statistical tests assume a two-sided significance level of 0.05.

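### Significance tests of baseline differences between randomised arms are uninformative; describe baseline by arm and adjust each outcome for its t0 value instead

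*Protocol article*

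**What the plan says.** The section on statistical methods for primary and secondary outcomes commits to baseline testing: "Between-group differences at baseline will be tested using analysis of variance (ANOVA". The sentence after it compares weight loss between the two groups, so the groups are most naturally the randomised arms. The same paragraph sets the level: "All statistical tests assume a two-sided significance level of 0.05". It also plans linear regression for all continuous outcomes and names no adjustment for baseline.

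On allocation, the sequence generation section says "Randomization took place at individual level, i.e. every single patient was assigned either to the IG or to the CG" and "A statistician who is not involved in the study generated the randomization list using computer-generated random numbers". The implementation section adds that "the random allocation sequence remained concealed from those enrolling patients into the study", and the concealment section describes central assignment.

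Baseline variables appear in two other places, neither tied to the baseline tests. The outcomes section lists sociodemographic characteristics and comorbidities as moderators. The section on additional analyses says "We will analyse the effect of sociodemographic and clinical variables on the primary outcome".

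**The concern.** A significance test asks whether a difference is larger than chance would produce. When chance alone formed the arms, that is already known, and the p-value informs only about possible subversion of the allocation. The protocol does not present the tests as a check of that kind.

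The result can mislead in both directions. A significant difference in a variable unrelated to weight loss looks like a problem and is not one. A non-significant difference in a strongly prognostic variable looks safe and may not be. What matters for the treatment comparison is the size of the imbalance multiplied by the variable's relation to the outcome, and the baseline p-value ignores the second factor. At stake are the reading of the baseline table and the precision available from routine adjustment for the starting value. The validity of the confirmatory test is not in question.

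**Working it through.** **Inputs from the protocol article.** Two-sided level 0.05; 50 per arm planned; SD 3.5 kg and power 80% (sample size section); 120 consenting (trial status), or 60 per arm if all were randomised and split equally.

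**Assumed, because not stated.** The number of baseline variables tested (5 to 20), their independence, the correlation ρ between a baseline variable and the outcome (0.2 to 0.7), and the mean weight.

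**1. The plan's own figure.** The sample size section says "a two-tailed *t*-test requires a total of 100 patients (50 per group". The 2% margin is not given in kg. At an assumed mean weight of 100 kg it is 2.0 kg. Reading 3.5 kg as the SD of individual weight change:

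n per arm = 2 × (1.960 + 0.842)² × 3.5² / 2.0² ≈ 48.1, so 49. The *t*-test calculation gives 49.05, so 50.

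The total of 100 reproduces. At 90 to 110 kg (1.8 to 2.2 kg) the normal approximation gives 60 to 40 per arm. The point below uses only the 50 per arm.

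**2. False-flag rate per test.** It is 0.05 by design. Simulation (200,000 replicates) gave 0.050 at both 50 and 60 per arm.

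**3. At least one flag among k independent tests.** 1 − 0.95^k:

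| k | Chance of at least one flag | Expected flags (0.05k) |
|---|---|---|
| 5 | 22.6% | 0.25 |
| 10 | 40.1% | 0.50 |
| 15 | 53.7% | 0.75 |
| 20 | 64.2% | 1.00 |

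**4. Smallest observed difference that is flagged.** In SD units it is t(0.975; 2n − 2) × √(2/n).

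- n = 50: 1.984 × 0.200 = 0.397
- n = 60: 1.980 × 0.1826 = 0.362

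**5. What can pass unflagged.** A baseline difference of 0.39 SD shifts mean weight loss by about ρ × 0.39 × 3.5 kg. That is 0.27 kg at ρ = 0.2, 0.68 kg at ρ = 0.5 and 0.96 kg at ρ = 0.7, beside an assumed target of 2.0 kg. Imbalances this close to the threshold are uncommon. The calculation shows only what the test would call acceptable.

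**6. If the test did decide adjustment.** Simulation with no treatment effect, 50 per arm, one baseline variable and 100,000 replicates per row. The test-then-adjust rule uses ANCOVA if the baseline p < 0.05 and the unadjusted test otherwise. The last column counts only trials with a flagged baseline difference.

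| ρ | Always ANCOVA | Test, then adjust | Unadjusted, given a flag |
|---|---|---|---|
| 0.2 | 0.049 | 0.049 | 0.070 |
| 0.3 | 0.050 | 0.048 | 0.101 |
| 0.5 | 0.049 | 0.043 | 0.181 |
| 0.7 | 0.050 | 0.035 | 0.328 |

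Always adjusting holds the level. The two-stage rule falls below it.

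**7. Precision from always adjusting.** Residual variance is multiplied by about 1 − ρ²: 0.96, 0.91, 0.75 and 0.51 at ρ = 0.2, 0.3, 0.5 and 0.7, for the cost of one degree of freedom.

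**The case against.** The strongest objection is that one sentence about a baseline table does little harm. Much of that stands.

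- **Covariate selection.** A reader might infer that the tests will steer the choice of covariates, since the regression names none. The protocol does not say so. It names candidate variables independently of the tests, in the outcomes section and under additional analyses. An exact covariate list is something a condensed article may leave to a full protocol or SAP that is not shown, so its absence is no fault here.
- **Inflated error.** A reader might infer a threat to the confirmatory level. Step 6 shows the opposite: even under test-driven adjustment, the overall rate is at or slightly below 0.05.
- **Chance of a flag.** The 22.6% to 64.2% range rests on an assumed number of independent variables. ANOVA suits continuous measures. Many sociodemographic items and comorbidities are categorical, and the chi-square sentence does not mention baseline. Weight with BMI, and lipids among themselves, are plausibly correlated, so the independence formula would tend to overstate the chance.
- **Late fixing.** Choosing adjustment now is not clean prespecification. The trial status section reports t1 complete, and the blinding section says the statistician was not blinded. This is correct, and the fix has to allow for it.

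The core point survives: the protocol commits to a test that is uninformative under its own allocation procedure. That commitment is stated in the article and is not a detail left to another document.

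**Conclusion.** The point holds in a limited form, as a minor improvement. Barring subverted allocation, each planned baseline test has a 5% chance of a false flag and no bearing on prognostic relevance. At 50 per arm it stays silent below an observed standardised difference of about 0.40 (0.36 at 60 per arm). These figures depend only on the stated level and the arm sizes. The chance of any flag depends on an unstated number of tests and should be read as a range.

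The documents do not support the stronger readings that the tests will select covariates, that they inflate the type I error, or that a flag would mean randomisation had failed. The loss lies in interpretation of the baseline table and in precision forgone. The gain from adjusting for baseline weight depends on a correlation that the protocol does not give, and it may be small at four weeks.

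**What to change.** 1. Delete the sentence on baseline testing. Present baseline data by arm descriptively (mean and SD, median and quartiles, or counts and percentages) without p-values.
2. State that the linear regression of each continuous outcome with a t0 measurement adjusts for that value, whatever the observed baseline difference. For the primary outcome this is baseline weight. With t0 in the model, analysing weight at t1 or its change in kg from t0 gives the same estimated group difference.
3. Report the date on which this adjustment was fixed, and show the unadjusted comparison beside the adjusted one, because t1 data are complete and the statistician is unblinded.

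The cost is a few sentences and one extra row in the results. The t0 values are already collected, and the sample size, randomisation and conduct are unchanged. The remaining limit is that a choice dated after t1 cannot carry the weight of one made before it, which is why both estimates should be shown.

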### Outcomes

The primary outcome of this study is difference in weight loss between baseline and end of inpatient rehabilitation after 4 weeks (short-term effectiveness). Secondary outcomes are difference in weight loss between baseline and 3 and 12 months after inpatient rehabilitation (long-term effectiveness), changes in blood pressure, fasting blood glucose and lipids and changes in diet as well as patients’ acceptance.

Weight, blood samples and clinical data are routinely collected as part of the initial and final examination. During inpatient rehabilitation, participants note daily periods of fasting as well as practicability (rating scale from 0 — very bad to 5 — very easy) in a fasting diary. They record all food and drinks, type of meal (breakfast, lunch, dinner, or snack), type of food and portion size. In addition, we carry out interviews about perceived advantages and disadvantages and acceptance with all participants in the IG.

After initial examination at admission (baseline, t0), three follow-up times are provided: final examination at the end of inpatient rehabilitation after 4 weeks (t1), as well as two follow-up times after inpatient rehabilitation after 3 and 12 months. The World Health Organization-Five Well-Being Index (WHO-5) is used for self-reported measure of current mental wellbeing at t0 and t1. A standardized follow-up examination (weight, blood samples) will be carried out by the family doctor at t2 and t3 for valid information. A financial incentive will be paid to family doctors for examination and data transfer.

Sociodemographic characteristics and comorbidities at baseline will be collected as moderating variables. Stable covariables (e.g. sociodemographic characteristics) will be collected only at baseline, while changeable variables will be measured at baseline and follow-up.

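### The plan offers Spearman's correlation as an alternative to the t-test for the primary mean difference in weight loss and does not say which method is primary

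*Protocol article*

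**What the plan says.** The Outcomes section defines one primary outcome for a two-arm trial: "The primary outcome of this study is difference in weight loss between baseline and end of inpatient rehabilitation after 4 weeks". The Statistical methods section calls the analysis of the intervention effect confirmatory and sets a two-sided 5% level. For the primary research question it states that "the mean difference in weight loss between the two groups is compared using analysis of variance (ANOVA), a two-tailed *t*-test, or Spearman’s correlation coefficient". The sentence ends "Spearman’s correlation coefficient, respectively", but it names only one comparison.

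Two other sentences in the same paragraph bear on the point:

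- "All continuous outcomes will be modelled using linear regression". No covariates are named, and it is not said whether this is the primary model.
- "Between-group differences at baseline will be tested using analysis of variance (ANOVA").

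The Sample size section takes the intervention to be effective if weight loss in the intervention group is at least 2% higher than in the control group. It uses an SD of 3.5 kg and concludes that "a two-tailed *t*-test requires a total of 100 patients (50 per group").

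Under Methods for additional analyses, covariates appear only in general terms: "We will analyse the effect of sociodemographic and clinical variables on the primary outcome". Baseline weight is not mentioned there.

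**The concern.** A confirmatory test needs one method fixed in advance. Here several are listed for one comparison, with no order and no rule for choosing.

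One of them does not fit the purpose stated in the same sentence. Spearman's coefficient is a unitless measure of rank association. It does not estimate a mean difference, so the 2% success criterion cannot be applied to it.

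The timing adds to the concern. The Trial status section reports that 4-week follow-up is complete, and the blinding section says that the statistician was not blinded. The primary data therefore existed, with allocation known, while the published text still left the method open. What is at stake is whether the nominal 5% level holds, and whether the reported result is a quantity that the plan's criterion can use.

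**Working it through.** **1. The plan's own figure.** Inputs from the Sample size section: SD 3.5 kg, two-sided alpha 0.05, power 0.80. The difference is stated only as 2%. The calculation needs kg, so 2% is read as 2.0 kg, which assumes a mean baseline weight of 100 kg that the article does not give.

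- Normal approximation: n per arm = 2 × (1.960 + 0.842)² × 3.5² / 2.0² = 48.1, rounded up to 49.
- Exact noncentral t: 49.05, rounded up to 50 per arm, 100 in total.

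The stated 100 is reproduced as a two-sample t-test, so the sizing assumes a comparison of means. How 2% relates to kg is a separate question.

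**2. How many distinct methods are listed.** With two groups, F = t² and the p-values coincide; in simulated data they agreed to rounding error. Linear regression on arm alone gives the same test again. The four method names therefore reduce to two procedures: a mean comparison and a rank correlation.

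**3. What Spearman's coefficient reports.** The same true difference of 2 kg (SD 3.5 kg, 50 per arm) gives an average coefficient that depends on the shape of the data:

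| Distribution of weight loss | Mean coefficient |
|---|---|
| Normal | 0.27 |
| Heavy-tailed (t, 3 df) | 0.37 |
| Skewed (lognormal) | 0.36 |

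The coefficient cannot be converted back to kg or percent without assuming a distribution.

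**4. Effect of leaving the choice open.** Simulation with 40,000 trials per setting, 50 per arm and SD 3.5 kg. The distributions are assumptions.

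| Data | Null: t-test rejects | Null: Spearman rejects | Null: either rejects | True 2 kg: the two disagree on significance |
|---|---|---|---|---|
| Normal | 5.0% | 4.9% | 6.0% | 5.0% |
| Heavy-tailed | 4.4% | 5.0% | 6.6% | 13.5% |
| Skewed | 4.6% | 4.9% | 6.8% | 15.3% |

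Each method alone stays at or below about 5%. The excess arises only if the better of the two is reported.

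**5. What baseline adjustment would add.** With equal SDs at both visits and a correlation ρ between the two weights, the variance of the baseline-adjusted estimate relative to the change-score estimate is (1 + ρ)/2. An SD of change of 3.5 kg implies ρ = 1 − 3.5²/(2 × SD²). The baseline SD is not in the article, so a range is shown:

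- SD 10 kg: ρ = 1 − 12.25/200 = 0.939; ratio 0.969, a gain of about 3%.
- SD 16 kg: ρ = 1 − 12.25/512 = 0.976; ratio 0.988, a gain of about 1%.

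These correspond to correlations between baseline weight and weight change of about √0.031 = 0.17 and √0.012 = 0.11. At correlations of 0.1 and 0.2 the required total is 98 and 96, so adjustment does not raise the number needed above 100.

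**The case against.** The best defence is that the intended test can be inferred. The Sample size section names the t-test, the analysis sentence speaks of a mean difference, and most of the listed methods are the same test. The word 'respectively' suggests a compressed sentence in which Spearman belonged to another question. The same section plans analyses of associations, fasting periods and calorie intake, where a rank correlation would fit. A drafting slip is at least as plausible as a deliberate menu. This stands as a reading of intent and limits the severity. It does not repair the text, which assigns Spearman to the primary comparison. An unseen analysis plan might fix the choice, but it would not make the published sentence correct.

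Three stronger readings are tempting, and the article does not support them:

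- **The type I error is above 5%.** This needs both methods to be run and the better p-value reported. The article says that 4-week data were complete and the statistician unblinded. It does not say that arms had been compared or that a method would be chosen from the data.
- **The inflation is larger than 6% to 7%.** Adding a baseline-adjusted model to the options gives 6.5% to 8.2% for assumed baseline-change correlations of 0.1 to 0.5, but the article names no such model.
- **Leaving out baseline weight is an error.** The outcome is a change from baseline, and an unadjusted comparison of changes is valid in a randomised trial. Covariates are also commonly left to the analysis plan.

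**Conclusion.** The point holds in a limited form. The analysis text lists, for one confirmatory mean difference, a method that cannot estimate it, and it gives no rule for which method is primary. The Sample size section points to the t-test, so the two sections should be reconciled.

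The consequence is modest: a null rejection rate of about 6% with normal data and up to about 6.8% with heavy-tailed or skewed data, conditional on a data-driven choice of which there is no evidence. At a true difference of 2 kg, the two procedures would disagree on significance in about 5% of trials with normal data and 14% to 15% otherwise. These figures assume 50 per arm, an SD of 3.5 kg and the simulated distributions. The sample size is unaffected. This should be fixed, but it does not undermine the design.

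The planned significance tests of baseline differences are a minor side point. Under proper randomisation they test a hypothesis known to be true, and they do not alter the primary estimate.

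**What to change.** Name one primary analysis: the between-arm mean difference in weight change from admission to the end of rehabilitation, from linear regression on randomised arm with baseline weight as covariate, reported with a 95% CI and a two-sided p-value. The scale (kg or percent) should be the one on which the 2% criterion is judged. The unadjusted t-test on change, already used for the sample size, would also be valid and would equally remove the ambiguity. Adjustment is preferred because its small gain costs nothing.

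Remove ANOVA and Spearman from the primary-question sentence. Keep Spearman for exploratory associations, such as those with fasting periods and calorie intake. Replace baseline significance tests with descriptive statistics by arm.

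Date the change, and state whether any 4-week comparison by arm had been made before it. The cost is a few sentences: no new data, and no change to the planned 100 patients.
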